#### **5.4 Co-enrolment guidelines**

Participants will be advised that they cannot enrol in any other trials during the period from screening to the final visit in the TaMoVac II study. If staff discover that a participant is enrolled on another study during this period, they must immediately contact the Principal Investigator or Clinical Research Coordinator of the study centre for advice. Decisions will be reviewed on a case by case basis by the TaMoVac II Trial Management Group Coordinating Committee (TMG) and participant safety will be the primary concern.

#### **5.5 Replacements in the Enrolment and Randomisation Lists**

Study participants who withdraw consent, are lost to follow up or are terminated from the vaccination schedule (e.g. because of pregnancy) should not be replaced in the randomisation list. The next consecutive assignment number on the list should be allocated to the next participant. The randomisation lists at each centre will be long enough to allow this. Whilst enrolment is ongoing, every effort will be made to achieve the planned number of 198 participants completing all five immunisation timepoints, and therefore slightly more than 198 may be enrolled.

## 6 TREATMENT OF PARTICIPANTS

### 6.1 Vaccine products

198 participants in six groups will receive three DNA or saline injections followed by two MVA-CMDR with or without CN54rgp140 adjuvanted with GLA-AF or saline injections in a schedule described in **Table 4 (section 6.4)**. Each participant will receive a total of five or seven immunisations.

### 6.2 Administration of vaccines

The immunizations will take place in an outpatient setting. Prior to each immunization participants will receive a baseline medical status check up including vital signs assessment to confirm the medical eligibility before vaccine administration. Safety lab procedures, urine analysis as well as HIV testing will be performed before vaccine administration. A pregnancy test for female participants will have to show negative results before each immunization.

The study pharmacist will draw the vaccines or placebos into the applicable syringes for the Zetajet devices in case of DNA vaccinations or into syringes for IM use in the case of the MVA and CN54 rgp140/GLA-AF vaccinations according to standardized operational procedures. Prior to use the vials will be thawed at room temperature. Thawed vials will then gently be swirled. Care will be taken not to shake or invert the vials.

Upon receipt of the syringes the study nurse/study doctor will deliver the vaccine.

The DNA vaccines/placebo will be administered in one or two injections ID using the needle free Zetajet® device at weeks 0, 4 and 12. The prepared syringes will be loaded into the Zetajet by the study pharmacist according to manufacturer's instructions. The Zetajet will be applied on the disinfected skin with light pressure. The study agent is expelled under pressure through a micro-orifice at high velocity in a fraction of a second. The study product should be administered as soon as possible after preparation. If this is not possible, the syringe may be stored under refrigeration (2 to 8°C) but the product must be administered within 4 hours after being drawn up into the syringe.

For study groups II and III electroporation using the Derma Vax™ device will be applied immediately after immunization over the injection site according to manufacturer's instructions and SOP. The Derma Vax™ DNA Electroporation System is a device that delivers a tightly controlled and documented series of electrical pulses to the skin between two arrays of 2 mm long needles 4mm apart.

The CMDR-MVA vaccine/placebo boosting will be administered IM using suitable needles and syringes at weeks 24 and 40 into the deltoid muscle of the left arm. The MVA will be given in a dose of  $10^8$  pfu infectious doses in 1 ml volumes (groups IA, IIA, IIIA) or 1 ml sterile saline will be injected (groups IB, IIB, IIIB).

The CN54rgp140 has to be mixed with the adjuvant GLA-AF for each of the two immunisations. This will be carried out by the pharmacists at each clinical research centre, under sterile conditions, according to standard operating procedures which are summarised as follows. The preparation will involve drawing 0.3mL of GLA-AF with a 0.5-1mL sterile syringe and transferring it into the cryovial containing 0.3mL of 0.5 mg/mL CN54 rgp140 solution. After gentle mixing of the two solutions, 0.4mL of this mixture will be drawn up using a 0.5–1 mL syringe, for administration. The vials containing the mixed formulation may be stored at room temperature during the period between mixing and administration; the mixture is stable for 2 hours. However, the rgp140/GLA-AF will be mixed just before each immunisation is about to take place, in sterile conditions in the clinic pharmacy and

passed to the study nurse for immediate use. The dose volume will be 0.4mL injected into the deltoid muscle of the right upper arm, using a 21–25 gauge needle long enough to reach deep into the muscle. The date and time of administration will be recorded in the CRF.

After each immunization participants will be closely observed at the clinic for 30 minutes. Vital signs and any local or systemic reaction will be recorded and participants will be seen briefly by the study doctor to document the post vaccination status. The needles, syringes and other materials will be disposed according to MNH/MMRC/CISPOC biohazard regulations. As with any parenteral vaccine, epinephrine and corticosteroids will be available for immediate use should an immediate hypersensitivity reaction, such as anaphylaxis, occur. Intravenous injections of vaccines will NOT be performed. Study vaccine will not be administered to individuals with hypersensitivity to any component of the vaccine. All immediate hypersensitivity reactions will be managed according to the developed SOP's.

Participants will be contacted by phone, home visit or clinical contact at the first day following immunization for a brief adverse reaction interview. Additionally, participants will complete diaries over events for the evening of the vaccination day and the 7 days following each vaccination. A diary card (**see Appendix 6**) will be provided after each immunization, with instructions and a full verbal explanation for volunteers to record local and systemic adverse events following immunization, as well as any medication taken. A folder with a diary card, thermometer and a ruler will be issued to each volunteer. The clinical team will provide contact information as well as a telephone number to call 24 hours, in order to assure contact with the study personnel if needed. Furthermore the study clinic will contact participants by phone within 48 hours after each immunization to assure their well being.

All participants will be asked to contact the study site in the case of adverse events of suspected grade 2 or more for evaluation. A decision to offer the participants a visit to the clinic should be made and documented in the source documents. All volunteers with suspected grade 3 or more should be seen by the study physician and documented in the source documents.

Safety follow-up visits are scheduled at week 2 and week 4 after each immunization visit. Diary cards will be reviewed and discussed at the scheduled 2 weeks follow-up visit after each vaccination. Diary entries will be transcribed after revision and discussion with the participant during the follow up visits after each vaccination into a Vaccine/Reaction Form.

### 6.3 Accountability for used and unused supplies

The PI must ensure that all IMP supplies are kept in a secure area accessible only to authorised individuals, and maintained in storage that guarantees the required temperatures.

#### Supply, storage, composition and labelling of the DNA vaccines

Vecura Company (Karolinska University Hospital at Huddinge, Stockholm, Sweden) will be responsible for bulk manufacture of the DNA vaccine, release testing and technical release of vialled product and labeling. All procedures will be according to Good Manufacturing Practice. The presentation is in liquid form which should be stored at –20 °C until use. Care will be taken not to break the cold chain.

The DNA plasmids were approved for human use on November 27th 2004 by the Swedish Medical Products Agency, (Svenska Läkemedelsverket), and the second revision of the protocol ethically cleared by the Swedish Internal Review board, (Regionala forskningsetiska kommittén) in December 2004. The new batch of the same plasmids will

need to have a further approval by the Tanzania Food and Drugs Authority (TFDA) and by the Pharmaceutical Department (Regulatory Authority) and Ministry of Health of Mozambique.

DNA will be packaged by Vecura. The trial products will be in vials pre-labeled according to standardized operating procedures. Each vial will be packed in a box labeled with the name of the clinical site and principal investigator, the storage details and the name of the supplier of the product, the name of the manufacturer, as well as the manufacture and expiry dates. The labels should also have the caption "for clinical trial only".

Cartons will be supplied to the designated pharmacist at MUHAS, MMRC and CISPOC for storing the used vials, labeled with the supplier, the name of the trial and protocol version, the name of the clinical site and principal investigator and the content of the material (DNA vaccine or placebo).

Having been manufactured by Vecura Company, the DNA vaccine will be supplied to the study by the Swedish Institute for Communicable Disease Control, [name], SWEDEN.

Sterile commercially available normal saline for human use will be used as the placebo.

#### *Supply, storage, composition and labelling of CMDR MVA*

Walter Reed Army Institute of Research (WRAIR), USA, will be responsible for the bulk manufacture of the clinical material, release testing, as well as the technical release of vialled product, and labeling. The full address of the manufacturer is: *Walter Reed Army Institute of Research (WRAIR), [name], Department of Biologics Research The Pilot Bioproduction Facility, [name] 20910, USA*. All procedures will be according to Good Manufacturing Practice. The presentation is in liquid form at 10^8 pfu per mL with an extractable volume of 1ml vials, which should be stored at -20 °C up to 3 months (-80°C if longer than 3 months) until use. Care should be taken not to break the cold chain. The product has already received approval from the USA Food and Drugs Authority (FDA), and the Swedish Medical Products Agency and will be presented to the TFDA for approval before use in Tanzania as well as to Regulatory Authority (Pharmaceutical Department) and Ministry of Health for approval before use in Mozambique.

Sterile commercially available normal saline for human use will be used as the placebo.

Each vial will be packed in a box labeled with the name of the clinical site and principal investigator, the storage details and the name of the supplier of the product, the name of the manufacturer, as well as the manufacture and expiry dates. The labels should also have the caption "for clinical trial only".

#### ***Supply, storage, composition and labelling of CN54 rgp140 GLA-AF***

CN54 rgp140 has been manufactured GMP by Polymun Scientific, Vienna, Austria. GLA-AF is manufactured and formulated GMP by the Infectious Disease Research Institute, Seattle, USA. The CN54 rgp140 will be supplied at 0.5 mg/mL, and the GLA-AF at 25 µg/mL (0.5mL/vial).

The products should be maintained in storage that guarantees the following temperatures:

- CN54 rgp140 protein at 2-8°C
- GLA-AF at 2-8°C

#### ***Conditions for Transport of material***

- CN54rgp140 should be shipped at 4°C.
- GLA-AF should be shipped at 4°C.

### **6.3.1 Measures to ensure cold-chain maintenance and storage**

Cold chain will be maintained by transportation packages according to manufacturer's instruction during shipment. This will be documented by temperature registration devices. The packing in Sweden will be divided into different parcels (one parcel for each site) to avoid re-opening the parcel before transporting to Mbeya site in Tanzania. Vaccines will be transported directly to Mozambique. The storage facilities have automatic backup generators to maintain storage temperature. At Dar es Salaam site, transport of the investigational product from the microbiology laboratory to clinic site will be done using study van in a container packed with ice bags. At the MMRC site investigational products will immediately be transferred and stored into the existing freezer at the MMRC pharmacy. At CISPOC the investigational products will immediately be transferred and stored in the existing freezer at the local pharmacy. The study pharmacy and study clinic are located within the same building.

#### *Transportation to the Mbeya Site*

The Pharmacist at Dar es Salaam site will be responsible for transporting the investigational products allocated to Mbeya site after being handed to him/her by world courier at Dar es Salaam Airport. Inventory of the consignment for Tanzania will be done by the Pharmacist at the Dar es Salaam site by filling the accountability form. Products allocated to MMRC will be shipped in their original boxes. The products will be stored according to specified storage conditions at MUHAS until the investigational products are transported on dry ice/cool packs to the Mbeya site. Transport to Mbeya will be done as early as possible to avoid delay or change of vaccination schedule for volunteers at the Mbeya site. The pharmacist at Mbeya site will receive the products handed to him/her by filling the handling documents before storing into the respective storage temperatures.

### **6.3.2 Dispensing records and disposal of unused product**

A record must be kept of all DNA, MVA-CMDR, CN54rgp140 and GLA-AF used during the trial. This will include the description (lot numbers and expiry dates) and quantity of IMP received at the trial site and date of receipt, as well as a record of when (date of administration) and to whom (subject number) it was dispensed.

The designated pharmacist will, upon receipt of supplies prior to commencement of the trial, conduct an inventory and complete a receipt, one copy of which will be retained at the site, and the original returned to the supplier (Swedish Institute for Communicable Disease Control, Sweden).

During the trial the pharmacist will be responsible for reviewing the dispensing log. On the day of the vaccination the study nurse/study doctor will fill in the Vaccine Request Form with the study visit number, the study site and participant code, the date as well as the vaccination number and randomized study group. The study pharmacist will check the vaccination number and date against the study number in the dispensing log. He will draw the vaccines or placebos into the applicable syringes for the Zetajet devices in case of DNA vaccinations or into syringes for IM use in the case of the MVA vaccinations according to standardized operational procedures. The study pharmacist will label the syringes with the study number, the site, the randomization group and participant code, date and time and hand them over to the study nurse/study doctor for injection. Labelling and dispensing log procedures will be counter checked by a second person. Upon receipt of the syringes the study nurse/study doctor will deliver the vaccine. The vial label will be cross-checked against the details on the vaccine request form by two individuals at the clinic (e.g. study doctor and study nurse) prior to the administration of the vaccine/placebo.

The Pharmacist will be responsible for ensuring that the used vials are recorded in the dispensing log at the end of the clinical session, and that they are placed in the appropriate

volunteer carton. All supplies (used and unused) will be retained at the trial site until the Sponsor gives instructions for their return/destruction in agreement with the supplier of the vaccines. At the end of the trial all used and unused vials will be checked against the inventory by the designated member of staff responsible for the inventory and the monitor before disposal on site according to MNH/MMRC/CISPOC biohazard regulations. Documentation will be provided to the monitor, Sponsor and supplier. During the trial, product accountability will be monitored by the vaccine request form, the dispensing log, the returns, the trial register and data collected on the clinical research forms.

The Sponsor and the PI will retain copies of the complete IMP accountability records and copies will be provided to the supplier of the vaccines.

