# 1 SUMMARY

## 1.1 Summary of trial design

### 1.1.1 Design

This is a randomised, three-centre, factorial design to assess a prophylactic HIV vaccine with the HIVIS DNA prime administered ID by the Zetajet® device with or without the Derma Vax™ electroporation device at a dose of 0.6mg in a concentration of 3mg/ml or in a concentration of 6mg/ml, followed by IM MVA-CMDR 10^8pfu per ml either alone or given at the same time as IM 100 µg CN54 rgp140 adjuvanted with 5µg GLA-AF.

Approximately 18 participants will be allocated to receive placebo. Clinical staff will not know who received placebo, but they cannot be blinded to the group, and will know whether the participant is allocated to electroporation, and receives one or two injections at each timepoint. Laboratory staff will be blind to the group and the allocation of placebo.

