### 5.2 Randomisation

There will be two randomization steps. During the first step prior to any vaccination, participants will be randomized according to different DNA immunizations (Groups 1, 2 or 3) and according to vaccine or placebo (A or B). During the second step prior to MVA, vaccination participants will be randomized according MVA (Group A1) or MVA plus gp140/GLA (Group A2) boosting maintaining the placebo affiliation (Groups B1 or B2). Randomisation lists will be drawn up under the supervision of [name]. These will be stratified by centre and gender to ensure a balance between the three active groups and matched placebos. The assignment for each subject will be placed in an envelope with a unique sequential number. Six sets of plain envelopes will be prepared, two for each centre (for males and females) and couriered to the Study Pharmacist for that centre who will take the prepared envelopes and put them in a box that is kept under lock.

The pharmacist will randomise participants accepted into the study, after receiving a copy of the participant's signed informed consent from nurse/doctor, by selecting the next consecutive envelope containing the vaccine or placebo assignment in accordance with the generated randomization list. The Pharmacist will make a record of the assignment and study number in a register held under lock. In the case a subject has to be replaced this is noted in the register; their assignment should not be given to the next volunteer to be randomized. The next volunteer should be allocated the next assignment. The Pharmacist will then inform the Study Nurse/Medical Officer at the clinic of the randomization group, I – III of the participant, but will not inform on whether this is vaccine or placebo. The Study Nurse/Medical Officer will record the group assignment in the study record of the participant's file. Procedures for the second randomisation will be similar. In addition to centre and gender, allocation will be stratified on the outcome of the first randomisation.

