### 5.3 Randomisation codes and unblinding

The vaccines will be kept in the department of Microbiology/Immunology at MUHAS, the study pharmacy at MMRC and the pharmacy at CISPOC under appropriate storage conditions according to manufacturer's specifications. The study pharmacist who has access to the envelopes will draw the study vaccine and the placebo into syringes and label them with the study number, the centre, the randomization group, I to III, date and time and hand them over to the study nurse/study doctor for injection. The study nurse/study doctor administering the vaccines, all other site investigators and lab personnel as well as the participants themselves will be blinded to the allocation of vaccine or placebo.

In the unlikely event that an investigator requests unblinding in order to manage an adverse event, the case will be discussed amongst the Trial Management Group. If a consensus to unblind is reached, then the Study Pharmacist will inform the clinician

managing the event of the allocation, and document this on the pharmacy register. Ideally this individual will be independent of the trial team. Laboratory personnel and other members of the trial team will remain blind to the allocation.

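### Section 6.3.2 has clinic staff check the vial label before each administration, in conflict with the vaccine-versus-placebo blind that sections 1.1.1, 5.2 and 5.3 place on them

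*Protocol*

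**What the plan says.** Three sections set the blind for clinic staff.

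- Section 1.1.1 (Design): "Clinical staff will not know who received placebo, but they cannot be blinded to the group".
- Section 5.2 (Randomisation): the pharmacist tells the nurse or medical officer the group, I to III, "but will not inform on whether this is vaccine or placebo".
- Section 5.3 (Randomisation codes and unblinding): the pharmacist draws up the product and hands over a syringe labelled with study number, centre, group I to III, date and time. On who may not know vaccine from placebo, it says: "The study nurse/study doctor administering the vaccines, all other site investigators and lab personnel as well as the participants themselves will be blinded".

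Section 6.3.2 (Dispensing records) repeats the hand-over of a labelled syringe and requires a second person to counter-check labelling and the dispensing log. It then adds a further check: "The vial label will be cross-checked against the details on the vaccine request form by two individuals at the clinic". Its examples of the two checkers are the doctor and the nurse of the study, and the check comes before the product is given.

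On presentation, the DNA supply text in section 6.3 says: "The trial products will be in vials pre-labeled according to standardized operating procedures". For the control it says: "Sterile commercially available normal saline for human use will be used as the placebo". The MVA supply text makes the manufacturer responsible for labelling and also uses commercial saline as placebo. The cartons that the pharmacist keeps for used vials are marked with "the content of the material (DNA vaccine or placebo").

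**The concern.** The examples given for the label check are the study doctor and the study nurse, who are the staff that section 5.3 blinds. If they read a vial that identifies its contents, they learn whether the participant is receiving vaccine or saline, starting with the first immunisation at week 0.

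Clinic staff make the clinical safety judgements. The primary safety endpoint (section 9.2.1.2) combines grade 3 or higher solicited events with events of any grade that lead to a clinical decision to stop immunisation. Under sections 7.5.5 and 9.5.3 the clinician's grade prevails over the diary card. Section 7.5.1 has the investigator judge relationship to vaccine, and section 7.6 lets the clinical investigator decide on discontinuation.

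Elsewhere the protocol protects this blind carefully. Unblinding to manage an adverse event requires consensus in the Trial Management Group (section 5.3), and HIV results go to the clinic only as infected or not infected (section 6.8). A routine check that discloses the product at every immunisation would undercut both safeguards.

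**Working it through.** The protocol states no figure to reproduce here. The check is a comparison of texts, followed by a count of how often the instruction applies.

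**1. Do the rules cover the same people?** Section 5.3 blinds the nurse or doctor who injects and all other site investigators. Section 6.3.2 has two people at the clinic do the check and offers the doctor and nurse as examples. The examples are not binding, but the breadth of section 5.3 means that other site investigators doing the check would be blinded too.

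**2. Would a vial label disclose the product?** The protocol does not give its wording, so this is an inference.
- The supply text describes pre-labelled vials for the DNA and makes the MVA manufacturer responsible for labelling. The supplier, manufacturer and expiry details are listed for the box, not the vial.
- The placebo for both is commercially available saline.
- No over-labelling, masking or matched placebo vial is described.

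On these facts a supplier-labelled vaccine vial and a commercial saline container would very probably be distinguishable.

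**3. Is vial a slip for syringe?** Compare the fields named in section 6.3.2.

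| Vaccine Request Form | Syringe label | Could a vial pre-labelled by the supplier carry it? |
|---|---|---|
| Site | Yes | Possibly |
| Participant code | Yes | No |
| Date of vaccination | Yes | No |
| Study group | Yes | No |
| Visit number | Not listed | No |
| Vaccination number | Not listed | No |

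Four of the six form fields appear on the syringe label. Five of the six could not be on a vial labelled before shipment. Sections 2.4.4.1, 5.3, 6.2 and 6.3.2 all describe syringes going to the clinic, and the pharmacist records and stores the used vials. A slip is therefore plausible.

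It is not certain. The same paragraph of section 6.3.2 uses syringe and vial as separate terms. Section 6.3.1 has product driven from the laboratory to the Dar es Salaam clinic without saying in which form.

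**4. What follows under each reading?**
- Read literally, the check very probably unblinds clinic staff.
- Read as a slip, staff who check the syringe depart from the written instruction, and staff who follow it risk the blind.

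The text needs correcting either way, and no other section reconciles the two rules.

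**5. Is the group on the form and syringe safe?** Section 5.3 limits it to I to III. Section 6.3.2 says only the randomisation group, and Table 4 lists study groups as IA, IB, IIA and so on, where A is vaccine and B is placebo. The limit should be repeated in section 6.3.2.

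**6. How often does the instruction apply?** There are five immunisation timepoints (weeks 0, 4, 12, 24 and 40) and 198 planned participants, 18 of them on placebo.
- All participants: 198 × 5 = 990 visits.
- Placebo recipients: 18 × 5 = 90 visits.

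These are upper counts if everyone completes the schedule. They measure exposure to the instruction, not bias.

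**The case against.** The strongest reply is that this is a one-word slip. The fields to be checked belong to a syringe label, only syringes are described as reaching the clinic, and a stock vial could not be matched to the request form. That is a good reason not to assume that sites would in fact be unblinded. It does not remove the contradiction, because sites work to the written text.

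A second reply is that the vial wording is unknown. That stands, and the disclosure is stated here as very probable, not as shown.

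A third reply concerns consequence, and most of it stands. A reader might infer that a vaccine-versus-saline safety comparison becomes open-label. The protocol names no such test. Section 9.3 assigns 180 participants to active product for the analysis and specifies two comparisons, among the three DNA groups and between the two boosts. Clinic staff already know the group and the number of injections by design, so a vial check adds little bias there.

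A reader might also infer that the saline arm loses its purpose. Section 9.3 gives it two: blinding laboratory and clinical staff, and reminding participants not to think themselves protected. Laboratory staff are not part of the clinic check, and nothing in section 6.3.2 shows participants the vial. Only the blinding of clinical staff is at risk.

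Some safety data also leave little room for judgement. Section 7.5.5 assumes that solicited events starting within 7 days are at least possibly related, and laboratory grades follow numeric limits in Appendix 8. Clinical grading, relatedness of other events and discontinuation decisions remain open to judgement.

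Finally, a two-person check at the point of administration can have its own safety value. The fix therefore keeps one.

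**Conclusion.** The point holds as an internal contradiction. Section 6.3.2 instructs clinic staff to check the vial label, while sections 1.1.1, 5.2 and 5.3 require the same staff not to know vaccine from placebo. Followed literally, the check would very probably reveal the allocation at up to 990 visits, including all visits of the 18 placebo recipients.

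That conclusion rests on two assumptions: that the text means vial, and that the vial label identifies the product. The first may be a drafting slip. The second is inferred from the supply text and the absence of any described masking.

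The harm is confined to the clinic-staff blind and to clinician-assessed safety data: clinical grading, relatedness and decisions to discontinue. The documents do not support a claim that the immunogenicity comparisons, the laboratory blind or the participant blind are compromised. The size of any bias cannot be calculated from the protocol.

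**What to change.** Amend section 6.3.2 as follows.

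- At the clinic, two people check the **syringe** label against the Vaccine Request Form.
- Vials stay with the pharmacy and are not shown to blinded staff.
- The pharmacist, with the second person who already counter-checks labelling and the dispensing log, checks the vial against the participant's assignment.
- The randomisation group on the syringe label and request form never shows the A/B (vaccine/placebo) code, in line with section 5.3.

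The pharmacy operating procedure should carry the same wording. The cost is a short text change in the protocol and that procedure. No extra staff are needed, because the second checker is already required, and the check at the point of administration is retained.
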